### Randomization

The main analysis will be the comparison between patients assigned to EMDR vs those not assigned to EMDR. The secondary analysis, only amongst patients assigned to EMDR, will be the comparison between patients assigned to active-MtCS vs patients assigned to sham-MtCS. Therefore, the individuals will not randomly be assigned to one of the three arms. Instead, the patients meeting the inclusion criteria will be randomized twice: first to EMDR vs non-EMDR, and then those in the EMDR group to active-MtCS or sham-MtCS. For the sake of brevity, only the randomization to EMDR vs non-EMDR is described here, because the randomization to active-MtCS vs. sham-MtCS is identical. The variables used for the randomization will be age, educational level, and pain intensity score. The first two patients will be randomly allocated to EMDR with *p* = 2/3. For each subsequent patient, the following biased coin algorithm will be applied: if a group includes at least two more patients than it would have to have to maintain the ratio 2 EMDR / 1 control, the patient will be randomly assigned to the other group with *p* = 0.6. Otherwise, there will be a simulation of the new patient as it was allocated to EMDR and calculate the between-group standardized difference in pain intensity variable, then simulate that the new patient is allocated to non-EMDR and recalculate the difference, and finally randomly allocate the patient to the group associated to the smallest difference with *p* = 0.6. This strategy decreases prognostic imbalances between groups because it decreases differences in potential co-founders, yet still includes randomization.

Once the randomization group has been obtained, the principal investigator (PI) of the study will inform the participants accordingly. If the participants have been assigned to the EMDR group, the coordinator will also contact the therapist responsible of the treatment.

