### Sample size calculation

The main tests of the study will consist of assessing whether patients assigned to EMDR show different levels in the pain intensity variable using a standard formula for two-tailed *t*-tests. The total sample size required to detect large to very large effect size differences (Cohen’s *d* ≥ 1) between two groups with a significance level of 0.05 and statistical power of 80% is 13 and 26. Assuming 15% dropouts, we will aim to randomize 45 patients, i.e., 15 + 30, so that after removing ~ 15% dropouts we would have approximately 13 + 26.

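### The 0.6 coins cannot hold a 2/3 EMDR share, so about 6 in 10 patients in the EMDR versus waitlist step are allocated without regard to pain, and baseline pain is balanced only modestly better than by chance

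*Protocol article*

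**What the plan says.** The protocol's Randomization section describes the EMDR versus non-EMDR step as follows.

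- Start: "The first two patients will be randomly allocated to EMDR with *p* = 2/3".
- Ratio check, from the third patient on: "if a group includes at least two more patients than it would have to have to maintain the ratio 2 EMDR / 1 control", then "the patient will be randomly assigned to the other group with *p* = 0.6". Pain plays no part here.
- Pain step, only if the check does not fire: "Otherwise, there will be a simulation of the new patient as it was allocated to EMDR and calculate the between-group standardized difference". The waitlist allocation is simulated in the same way, and the rule is then to "randomly allocate the patient to the group associated to the smallest difference with *p* = 0.6".
- Stated purpose: "This strategy decreases prognostic imbalances between groups because it decreases differences in potential co-founders".

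The section says "The variables used for the randomization will be age, educational level, and pain intensity score", but pain is the only one of the three that enters the calculation it describes. The second randomization (active versus sham) is said to be identical and is not written out. The Sample size calculation section says "we will aim to randomize 45 patients, i.e., 15 + 30". The Data analysis section adds baseline pain as a covariate.

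**The concern.** The only reason given for an elaborate allocation rule is better prognostic balance. The variable it balances is the baseline value of the main outcome. If the balancing step is idle for most patients, the rule gives little of what it was chosen for.

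The cause lies in the probabilities. A 0.6 coin towards EMDR yields fewer EMDR allocations than the 2/3 that the ratio requires, even when it is pushing towards EMDR. The pain step favours either group about equally often, so it allocates at about 1:1, further still from 2:1. Both steps push the waitlist over quota. Once it is two over, the ratio check takes precedence and is too weak to bring the groups back, so pain stays out of use. The same miscentred coins also cause the shortfall from the planned 30:15. Loss of pain balance is largely a second consequence of that one defect.

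**Working it through.** **Plan's own figures.** The stated target is 30 + 15 = 45. With 15% dropout, 0.85 × 45 = 38.25, close to the required 13 + 26 = 39. By the noncentral t, 13 + 26 has power 0.818 for d = 1 at two-sided 0.05, so that requirement reproduces. The protocol gives no figure for expected pain imbalance or for the share of patients whose pain is consulted, so these were simulated.

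**Inputs from the Randomization section.** First two patients: P(EMDR) = 2/3. Trigger: a group at least 2 over its share of the total (two-thirds or one-third of those already allocated). Coin: 0.6 in both steps. N = 45. *Assumptions:* pain is normally distributed (a uniform 4 to 10 distribution gives nearly the same results), and the standardized difference is absolute, with pooled SD. Several thousand runs per setting.

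**Why the check keeps firing.** The expected growth of the EMDR shortfall per patient is 2/3 minus P(EMDR).

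- Ratio check firing for waitlist excess: 0.667 − 0.60 = +0.067.
- Pain step: 0.667 − 0.50 = +0.17.

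Both are positive, so the shortfall grows in either step. On the literal reading about 99% of the triggers are for waitlist excess.

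**How often pain is used.** The check fires for about 26 of patients 3 to 45 (61%). Adding the first two gives 28/45 = 62% allocated without pain. Among the last 15 patients it is about 84%. Two other readings of the trigger give 67% (rounded quota) and 77% (excess counted against the other group's size), so the literal reading is the mildest.

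**Group sizes, as a cross-check.** 2 × 0.667 + 26 × 0.60 + 17 × 0.50 = 1.3 + 15.6 + 8.5 = 25.4 in EMDR. The simulation also gives 25.4, so the split is about 25:20.

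**Balance of baseline pain (difference in SD units).**

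| Rule | No. of 43 bypassing pain | Mean EMDR | SD of difference | P(>0.3) | P(>0.5) |
|---|---|---|---|---|---|
| As written | 26 | 25.4 | 0.26–0.27 | 24–25% | 6% |
| Same rule, pain ignored | – | 25.4 | 0.30–0.31 | 32–33% | 10% |
| Plain 2:1 | – | 30 | 0.32–0.33 | 34–35% | 11–12% |
| Ratio coin alone raised to 0.8 | 18 | 28.1 | 0.23 | 19% | 4% |
| Ratio check first, 0.80/0.53 in both steps | 10–11 | 30 | 0.18–0.19 | 10% | 2% |
| Pain always consulted, 0.77/0.57, shifted by ±0.1 | 0 | 30.2 | 0.18 | 10% | 1.5% |

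**Effect on the adjusted estimate.** For a baseline difference d, adjustment multiplies the variance by about 1 + d² / [(1/n₁ + 1/n₂)(N − 2)]. At 25:20 the denominator is 0.09 × 43 = 3.87. With d at 0.26 the inflation is 0.0676/3.87 = 1.7%. With d at 0.18 it is 0.0324/3.87 = 0.8%. The loss is about 1%.

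**The case against.** Four objections carry weight.

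1. *The stated benefit is true.* A reader might infer from the branch counts that pain is balanced no better than by chance and that the protocol's sentence is false. The figures do not support that. Differences above 0.5 SD fall from about 10–12% to 6%, and those above 0.3 SD by about a quarter. The protocol promises a decrease without saying how large, and there is one.
2. *Putting the ratio check first is not the main fault.* A reader might blame the order of the steps. But keeping that order and recentring both coins cuts the bypass from 26 to about 10–11 of 43 and comes close to the balance obtained when pain is always consulted. Checking the ratio first is an ordinary choice. Raising only the ratio coin leaves 18 of 43 bypassing pain, because the pain step still allocates at about 1:1.
3. *It does not cover both randomizations.* If active versus sham targets 1:1 (an assumption, since that step is only called identical), a 0.6 coin is adequate. The check then fires for about 22 to 24% of patients, and at n = 30 the mean absolute difference is 0.21, against 0.30 with pain ignored.
4. *Practical harm is small.* Baseline pain is a covariate. No bias and no effect on the type I error has been shown, and none should be inferred.

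All four stand, and they limit the point. They do not remove it: in the main comparison the written probabilities work against both the rule's stated purpose and its stated ratio.

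**Conclusion.** The point holds for EMDR versus waitlist only. On the mildest reading of the trigger about 6 in 10 patients are allocated without regard to pain, and up to 77% on another reading. Balance is modestly better than chance (SD about 0.26 against 0.30–0.32) and well short of what the scheme could deliver (about 0.18). The shortfall follows largely from the same coins that give about 25:20 instead of 30:15. It is a weakness of design efficiency and credibility, costing about 1% in the precision of the adjusted estimate. The balance figures are simulation results and rest on an assumed pain distribution and a pooled-SD difference.

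**What to change.** Before the restart, do one of the following.

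- **Recentre the coins and keep the ratio check first.** In both steps use P(EMDR) = 0.80 when the step favours EMDR and 0.53 when it favours the waitlist (average 0.665). Simulated result: about 30:15, SD 0.18 to 0.19.
- **Consult pain for every patient.** Use P(EMDR) = 0.77 if EMDR gives the smaller absolute pain difference and 0.57 if not. Add 0.1 when the waitlist is two or more over its share, and subtract 0.1 when EMDR is. Simulated result: about 30:15, SD 0.18.

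Either way, define the trigger as excess over a group's share of all patients allocated so far. State the target ratio of the active versus sham step and centre its probabilities on that target.

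**Cost.** A few lines in the randomization program and a reworded paragraph. The Trial status section says the trial is to restart from the beginning, so no retained allocation is affected. The next allocation becomes somewhat easier to guess, with probabilities up to 0.80 under the first option and 0.77 + 0.10 = 0.87 under the second. A separate institution runs the randomization, which limits that risk. Restoring 2:1 also gives up the accidental gain of a more even split: 1/n₁ + 1/n₂ rises from 0.090 at 25:20 to 0.100 at 30:15. In return, active versus sham has the planned 30 patients, not about 25.

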### Interventions

#### Eye movement desensitization and reprocessing (EMDR)

EMDR therapy will consist of a maximum of 20 individual 60-min sessions of psychotherapy, principally using the EMDR protocol for FM [60]. This protocol begins by gathering information about all aspects of the patient related to FM (phase 1) and helps create a hierarchy of the targets that are going to be processed during the sessions (phase 2). The following phases (3 to 8) follow the same steps as the EMDR Standard protocol [61]. The protocol is briefly described below:
Patient history: The therapist collects information about the patient’s biography in relation to the following aspects: history of FM, psychological trauma history, pain as a trauma, and pain triggers. These memories will be therapeutic targets in the following sessions. Treatment aims will be agreed between the patient and therapist.Preparation: The patient will receive an explanation of the EMDR approach and how the therapy functions. The therapist will get to know the patient’s personal resources and check the patient’s preferences with regard to bilateral stimulation. If eye movements are not well tolerated, tapping or auditory tones will be used. Positive resources for emotional regulation and self-care will be installed.Assessment: The therapist will help the patient focus on a traumatic event selected from the first phase. The patient will select the image that represents the most traumatic part of the event and the positive and negative cognitions associated with the memory, as well as the validity given to these cognitions using the Validity of the Cognition Scale (VoC; ranging from 1 signifying “completely false” to 7 signifying “completely true”). Emotions, sensations in the body, and the level of distress generated by the memory will also be registered by using the Subjective Units of Disturbance scale (SUD; ranging from 0 indicating “neutral or no distress” to 10 indicating “maximum distress”).Memory desensitization: The patient will focus on the traumatic image and will associate it with the negative cognition, emotions, and bodily sensations reported in the previous phase. At the same time, the therapist will apply bilateral stimulation and the patient will observe any changes. After every set, the patient will inform the therapist about every change that has occurred. The role of the therapist will be to guide and accompany the patient during the processing until the SUD reaches 0.Installing the positive cognition: The patient now focuses on the original memory and is asked to associate it with the positive cognition identified in the third phase. Bilateral stimulation will also be used to install the cognition.Body scan: When the fifth phase is done, the patient will be asked to keep the memory and positive cognition in mind, and to scan their body for any sensations. If there is any negative sensation, bilateral stimulation will be applied until the sensation disappears. If there are only positive sensations, these will be installed through sets of bilateral stimulation.Closure: When the session finishes, the therapist will explain that in the following days new material (such as new associations or memories) can arise, in which case the patient should register it for the following session.Reevaluation: In the next session, the therapist will assess the state of the distress caused by the memory processed during the last session. If the memory has been correctly processed and no longer causes distress, the therapist will then proceed to treat other memories following the same protocol.

When a patient appears to suffer intense pain during the regular EMDR session, and the pain is threatening the patient’s processing, the CP protocol [62] will be used. Here, the target chosen is the current pain referred to by the patient. The main differences between the FM and the Pain protocols are the following: in phase 3, the patient must describe the pain felt and draw a representation of it, as well as assigning it personal characteristics; after phase 6, when improvements in levels of pain occur, the patient alongside the therapist will build a positive resource in order to reinforce the positive progress. It will then be followed by phases 7 and 8 of the standard protocol mentioned. Below is a brief description of the CP protocol:
Check that the patient’s pain is at a tolerable level by asking the patient to make a subjective assessment of their pain, evaluating their attitude to it, and ensuring that their pain is sufficiently controlled.The medical diagnosis and the patient’s attitude toward it, including degree of acceptance, are reviewed.The targets for EMDR reprocessing, and the treatment objectives (for example, pain relief or greater control over pain), are identified and put in order of priority and used to draw up a treatment plan. As pain is in many cases related, either directly or indirectly, to a traumatic or stressful event, these are treated first using the standard EMDR protocol explained above.Next, each pain point is treated separately with the goal of helping the patient to relax and to notice changes in pain sensations. Bilateral stimulation is applied while the patient focuses on either current pain or a memory of pain. After each set, the patient explains their pain experience, and whether changes have occurred in the severity of the pain, its type, or where it is felt. The sets of bilateral stimulation are continued until the patient notices a positive change.Finally, the patient is assisted in developing psychological pain management resources, achieved by the cognitive integration of the positive changes in pain sensations. First, the positive change is linked to an image, and this is reinforced through sets of bilateral stimulation. The patient then chooses a word to associate with the positive change, and this is reinforced through further sets of bilateral stimulation. The patient can then bring to mind the positive image and associated word and self-apply bilateral stimulation when they feel pain in the future, thus giving the patient pain management resources.

It is important to mention that this psychological intervention does not usually cause any risk to the health of the participants. However, due to remembering and reprocessing past traumatic experiences, it is possible that emotional discomfort will be felt during the evaluation and the therapeutic sessions. This discomfort usually disappears before the end of a session or, in exceptional cases, can also continue in the following day. If the discomfort continues, a new session with the patient should be immediately scheduled to assist her.

Should adverse effects other than those related to emotional discomfort from the therapeutic sessions occur, these shall be reported to the PI of the project. Additionally, if it is likely considered that EMDR was the cause, they will also be reported to the Ethics Committee department and relevant regulatory bodies, as required, indicating expectedness, seriousness, severity, and causality. However, as no problems that are detrimental to the participant are anticipated, no interim analyses or formal stopping rules have been planned.

Throughout the duration of the study, no participant may receive trauma-focused therapy sessions in parallel.

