**Methods:**

Forty-five patients with FM and a history of traumatic events will be randomly allocated to Waiting List, EMDR + active-MtCS, or EMDR + sham-MtCS. Therapists and patients will be kept blind to MtCS conditions, and raters will be kept blind to both EMDR and MtCS. All patients will be evaluated at baseline, post-treatment, and follow-up at 6 months after post-treatment. Evaluations will assess the following variables: sociodemographic data, pain, psychological trauma, sleep disturbance, anxiety and affective symptoms, and wellbeing.

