**Fig. 2 Fig2:**
[figure not shown]
Multifocal transcranial Current Stimulation (MtCS) montage

In the case of patients who have been prescribed medication with effects on the nervous system, such as antidepressants, anxiolytic drugs, anticonvulsants or atypical antipsychotics, an individualized follow-up of the clinical outcomes will be carried out to ensure that there is no interaction with the brain stimulation [28]. Although the application of MtCS is painless, in the event that a participant, due to her medical condition, feels marked pain or very significant discomfort due to the application of the stimulation and asks to stop the stimulation, this decision will be respected and the participant will receive EMDR treatment only. Again, if other different adverse effects than those mentioned above occur, they will be reported to the PI, and, in the event they are considered to be related to MtCS, also to the Ethics Committee department and relevant regulatory bodies as required, indicating the expectedness, seriousness, severity, and causality of the adverse effect. However, as has been mentioned previously, no problems that are detrimental to the participant are anticipated, meaning no interim analyses or formal stopping rules have been planned.

During the time of the study, no participant may receive MtCS sessions in parallel.

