Anxiety and depression will be assessed using the following scale:
Hospital Anxiety and Depression Scale (HADS) [81], Spanish validation [82]. The HAD was created for detecting the presence of anxious and depressive disorders. It contains 14 items, 7 for each of the subscales (anxiety and depression), which can be rated from 0 to 3. A punctuation higher or equal to 11 indicates presence of affective disorder.

Quality of sleep will be assessed using the following scale:
Athens Insomnia Scale (AIS) [83], Spanish validation [84]. The AIS is a self-administered scale based on the ICD-10 criteria for insomnia. It measures sleep difficulties suffered over the previous three nights. It consists of 8 items evaluating sleep induction, awakenings during the night, final awakening, total sleep duration, sleep quality, wellbeing, functioning capacity, and sleepiness during the day. It is scored from 0 to 24 and higher scores mean greater difficulties.

Wellbeing will be assessed using the following scale:
Satisfaction With Life Scale (SWLS) [85], Spanish validation [86]. The SWLS is a 5-item self-administered scale measuring global cognitive judgment of satisfaction with one’s life. The items can be rated from 1 to 5, and lower scores indicate lower satisfaction.

All patients will be clinically evaluated at baseline/enrollment (*t*_1_), post-treatment (*t*_2_), and follow-up evaluation at 6 months from post-treatment (*t*_3_) (see Tables 1, 2, and 3). Personal participant data will be numerically coded and kept in a database in the Centre Forum Research Unit, who will be responsible for data maintenance and safety. Only the researchers involved in this trial will have access to this data. The database will contain the information of both the participants who finish the study as well as those who drop out, along with the corresponding causes for not completing the study. The Centre Forum Research Unit will be responsible for creating and maintaining the database.

**Table 1 Tab1:** Measurements to evaluate pain and FM impact

Clinical variable	Measurement interview/self-report	***t***_**1**_ Baseline	***t***_**2**_ Post-treatment 6 months	***t***_**3**_ Follow-up 12 months
Pain intensity	VAS pain	x	x	x
Pain disability	PDI	x	x	x
FM impact	FIQ	x	x	x

*VAS pain* Visual Analog Scale for pain, *PDI* Pain Disability Index, *FIQ* Fibromyalgia Impact Questionnaire

**Table 2 Tab2:** Measurements to evaluate psychological trauma symptoms

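### The adverse-effect rules exempt from reporting the harms the protocol itself names (EMDR session distress, and pain or discomfort that ends MtCS), and no other stated route captures them

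*Protocol article*

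**What the plan says.** All the relevant text is in the protocol article, under Interventions.

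- **EMDR, foreseen harm.** Because traumatic memories are reprocessed, "it is possible that emotional discomfort will be felt during the evaluation and the therapeutic sessions". The article says this usually passes within the session and exceptionally lasts into the next day. "If the discomfort continues, a new session with the patient should be immediately scheduled to assist her".
- **EMDR, reporting rule.** "Should adverse effects other than those related to emotional discomfort from the therapeutic sessions occur, these shall be reported to the PI". Those thought likely to be caused by EMDR also go to the Ethics Committee and regulators, with a grading that includes seriousness, severity and causality.
- **MtCS, foreseen harm.** Stimulation is described as painless, but the text provides for a participant who "feels marked pain or very significant discomfort due to the application of the stimulation and asks to stop the stimulation". In that case "this decision will be respected and the participant will receive EMDR treatment only".
- **MtCS, reporting rule.** "if other different adverse effects than those mentioned above occur, they will be reported to the PI", with the same onward reporting if the effect is considered related to MtCS.
- **Oversight.** Research setting rules out a Data Monitoring Committee because the intervention is low-risk. The EMDR and MtCS subsections plan no interim analyses or stopping rules because no detrimental problems are foreseen.

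**The concern.** The two rules begin by setting aside the very reactions that the article has just named. The EMDR exemption covers anything related to emotional discomfort, however severe or long-lasting. The MtCS exemption, read literally, falls on the severe end: a mild sensation is a different effect and is reportable, while pain that ends stimulation has been mentioned above and is not.

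Three things are at stake.

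- The article describes the trial as exploratory and as informing a larger one, so tolerability by arm is among its useful products.
- The stimulator is, by the article's own account, an investigational device under US law, and all participants have current trauma symptoms together with depression or anxiety.
- The principal analysis is by intention to treat. The number of patients who stopped stimulation in each MtCS arm is therefore needed to interpret any difference between active and sham.

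**Working it through.** No arithmetic applies, because the point concerns which events the rules cover. The check takes each foreseen event through every route the article states.

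**Step 1: what each reporting rule covers**

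| Foreseen event | Stated handling | Reported to the principal investigator? | Limit on the exemption |
|---|---|---|---|
| Emotional discomfort related to EMDR sessions | Extra session if it continues | No, expressly excluded | None on severity, duration or seriousness |
| Pain or discomfort that makes a patient stop MtCS | Stimulation stops, EMDR continues | No, on a literal reading | None stated |
| Milder or different effects of MtCS | None stated | Yes | Not applicable |

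Reporting to the Ethics Committee and regulators starts from the same reduced set. An exempt event is therefore removed before its seriousness or expectedness is graded.

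**Step 2: whether another stated route picks these events up**

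1. *Planned assessments.* The abstract says "Evaluations will assess the following variables: sociodemographic data, pain, psychological trauma, sleep disturbance, anxiety and affective symptoms, and wellbeing". Adverse effects are not listed there, and Tables 1 to 3 have no row for them.
2. *Symptom scales.* VAS pain, IES-R, SUD, DES and HADS are taken at baseline, post-treatment (6 months) and follow-up (12 months). They measure symptom level at visits six months apart. They do not count reactions in up to 20 sessions, nor attribute them to EMDR or MtCS.
3. *Causes of non-completion.* The database holds dropouts "along with the corresponding causes for not completing the study". A patient who stops MtCS goes on with EMDR, so she has not dropped out and need not appear there.
4. *Follow-up of patients on medication acting on the nervous system.* This is confined to those patients and aims to rule out an interaction with stimulation. No record of stimulation pain is stated.
5. *Case report form.* The items that Outcomes lists for it are demographic, history and treatment variables. Adverse effects are not among them, though the form itself is not shown.

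**Step 3: consequence**

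None of the five stated routes is bound to capture either exempt event. Active and sham share the same sessions and the same blinding of patients and therapists, so they offer a like-for-like comparison of these reactions, but the article states no data source for it. The low-risk premise behind the oversight arrangements is likewise left without a stated check on the named harms.

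**The case against.** **Reporting is not recording.** A reader might infer that these harms will go uncounted altogether. The text does not say so. It limits what is sent to the principal investigator and onward, and an unseen case report form or full protocol may record more. This stands, and the point is confined to reporting and to the routes the article states. It does not remove the point, because the article lays down an explicit exclusion twice and does not merely leave out a detail.

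**Stimulation pain is a contingency.** A reader might take it as the expected harm of MtCS, or take all MtCS discomfort as exempt. Neither is supported. The article calls the procedure painless, provides for the event only should it occur, and leaves milder sensations reportable. The reference to effects mentioned above is loose, which is itself a reason to rewrite it.

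**The committee decision has its own reason.** It rests on low risk. The expectation of no detrimental problems supports only the absence of interim analyses and stopping rules. The two should not be merged.

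**Lasting harm would show.** Persistent worsening would appear in the symptom scales by arm. This is partly right, but those scales cannot separate a session reaction from the course of the illness.

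**Removing the exemptions outright would overload reporting.** EMDR deliberately evokes distress and works until it subsides. With 30 EMDR patients and up to 20 sessions each, 30 × 20 = 600 sessions could generate routine reports. Waitlist patients have no sessions to match, and raters who asked about session or stimulation discomfort could be unblinded. All of this stands and shapes the fix.

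**Conclusion.** The point holds as a defect in the stated reporting rules. The EMDR exemption is plain on the page and unlimited in severity and duration. The MtCS exemption depends on reading the reference to effects mentioned above literally. No other route in the article fills the gap, so followed as written there is no stated basis for comparing active with sham MtCS on these reactions or for testing the low-risk premise.

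The size is qualitative. A zero-event confidence bound could be computed for any unreported event, but it would say nothing specific about this plan. The conclusion assumes that the article's rules are the operative ones. If a fuller document already records these events by session, what remains is to bring the published wording into line. The change is worth making before the restart that Trial status foresees.

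**What to change.** Reconcile the two EMDR paragraphs (foreseen discomfort, adverse-effect reporting) and the MtCS paragraph after Figure 2, so that:

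1. Emotional discomfort related to sessions, and pain or discomfort from stimulation, are recorded at each session with severity, duration and relatedness. Every stop of stimulation for pain or discomfort is recorded as an event.
2. The record is made by the staff who deliver the sessions, who already know that EMDR is being given, and not by the raters, who must stay blind to EMDR and MtCS.
3. Results are tabulated by randomised arm. Active versus sham is the like-for-like comparison. Waitlist is shown with a note that it has fewer contacts and so fewer chances to detect events.
4. The exemption is limited to expedited reporting of non-serious expected events, so that serious or persistent events of these kinds still reach the principal investigator.
5. The phrase about effects mentioned above is replaced by a named list.

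The clinical handling of these events is not touched.

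The cost is one case report form line per session (at most 600 in the EMDR arms), one table by arm, and more mild expected events to log.
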